#### Data collection (basal visit)

During the basal visit all the necessary data will be collected using an ad hoc questionnaire (Supplementary data 1) that includes: sociodemographic variables, clinical history of comorbidities and risk factors associated with tobacco use, basic physical examination, lifestyle and habits, smoking habit and characteristics about it, pregnancy variables. Different variables are specifically detailed in Table 2.

**Table 2 Tab2:** Variables description and registration

**Type of variable**	**Description**	**Description**
**Sociodemographic variables:**		
Age	Date of birth (dd-mm-yyyy)	Basal
Gender	Feminine; Masculine; Non-binary	Basal
National culture	Western; Oriental; Arab; South American; North American	Basal
National culture	A single; In a Heterosexual couple; In a Homosexual couple; Partnered with children	Basal
Social class	British Registrar general's Social Classification	Basal
**Basic physical examination: **		
Weight	Kg	Basal and follow-up
Height	cm	Basal
Blood pressure	mmHg	Basal and follow-up
**Lifestyles and habits: **		
Physical activity	hours/week	Basal and follow-up
Alcohol consumption	units/week	Basal and follow-up
**Clinical history of comorbidities and risk factors associated with tobacco use:**		
Hypertension; Diabetes mellitus; Ischemic heart disease; Cerebrovascular accident; Peripheral arterial disease		Basal
**Smoking habit**		
Nicotine dependence level	Fagerström test: Low ≤ 3; Medium 4-6; High ≥7	Basal
Motivation	Richmond test: Low ≤ 4; Medium 5-6; High ≥ 6	Basal
Stage of change	Prochaska and DiClemente model : Pre-contemplation; Contemplation; Preparation; Action; Maintenance; Relapse	Basal
Consumption before pregnancy	Cigarettes/day	Basal
Current consumption	Cigarettes/day	Basal and follow-up
Type of tobacco consumption	Cigarettes; Cigars; E-Cigarettes; Smokeless Tobacco; Hookah; Pipes; Others	Basal
Age at starting smoking	Years old	Basal
Previous quit attempts	Number	Basal
Reasons for relapse	Weight gain; Stress; Nicotine withdrawal symptoms; Others	Basal
Use of drug therapy or other methods for smoking cessation during the study	Nicotine replacement therapy; Bupropion; Varenicycline; Others	Basal and follow-up
Smokers in the family	Yes; No	Basal
**Pregnancy variables**		
EDD	Estimated Date of Delivery	Basal
TPAL code	Term births; Premature births; Abortions; Living children	Basal
LMP	Last Menstrual Period	Basal
**Biochemical measures during pregnancy follow-up**		
Basic blood tests	Hemogram components (Leukocyte count, erythrocyte count, hematocrit, hemoglobin, mean corpuscular volume, mean corpuscular hemoglobin); Platelets count; Glucose levels	Follow-up (in general 1/trimester)
**Smoking habit follow-up**		
Current consumption	Cigarettes/day	Follow-up
Relapse	Yes; No	Follow-up
Date of Relapse	dd-mm-yyyy	Follow-up
eCO test	<10 ppm, smoking abstinence; >10 ppm, active smoking	Follow-up/End
Cotinine test in urine	<100 ng/ml, smoking abstinence; 100 - 500 ng/ml, occasional smoker; > 500 ng/ml smoker	End
**Birth Indicators **		
Date childbirth	dd-mm-yyyy	Follow-up
Type of childbirth	Eutocic; Dystocic	Follow-up
**Newborn health indicators**		
Body weight	kg	Follow-up
Height	cm	Follow-up
Cranial perimeter	cm	Follow-up
Apgar test	Score: Normal condition 7-10; Moderately depressed 4-6; Severely depressed 0-3	Follow-up
**Data about application usage:**		
Number of days within the app; Number of different days connected; Chat usage		End

The researchers in this study believe that it is appropriate to consider the gender of participants as an interesting factor of study. For this reason, the distinction between gender and sex has been taken into account during the drafting of this study protocol, considering sex as a biological condition and gender as a social perception.

#### Randomization

All participants included in the study will be assigned to the control or intervention group (IG) in a 1:1 ratio using the EPIDAT programme (General Directorate of Innovation and Public Health Management, Xunta de Galicia, Spain; version 3.1). The randomisation will be carried out by the primary care centre and centralised from the Research Support Unit of IDIAP Jordi Gol of Tarragona with a simple numerical randomisation ratio.

### Description of the intervention

All participants will received health education and counselling on smoking cessation, following the 5A’s strategy, which includes five steps: Ask, Advise, Assess, Assist and Arrange. Moreover, each participant, with the support of the referral midwife, will planned a specific day to quit smoking (D-Day).

In addition, participants assigned to the IG will be invited to download the Tobbstop App, either from the Play Store (Android) or Apple's App Store (iOS), along with an explanation of how to use it and the access code will be provided. The IG will have access to the Tobbstop App from 7 days before D-day to 90 days after. Tobbstop App has been successfully tested in the general population [20]. For the present study the contents have been updated and adapted to the study population (pregnant smoker), as described in Supplementary data 2.

### Follow-up and data collection

During the pregnancy period, follow-up of the study will be adapted according to the pregnancy calendar in the ASSIR. If participants did not attend the follow-up visit in the ASSIR, they will be called by phone to ensure participant’s continuance with the study and to evaluate smoking habit (see Fig. 2). If telephone interviews coincide with a pregnancy visit in the ASSIR, the telephone call will be avoided. After the birth, telephone interviews will be planned monthly to evaluate smoking habits in the long term.

**Fig. 2 Fig2:**
[figure not shown]
Chronogram of planned follow-up visits during the study and according to the usual follow-up pregnancy visits. LMP, last menstrual period; EDD, estimated date of delivery; gw, gestational week; ppw, postpartum weeks; w,week; m,month. † In case that usual follow-up visits were not possible, telephone interview will be conducted

Smoking habits will be assessed by questionnaire in the scheduled pregnancy follow-up visits and by telephone interviews. Exhaled carbon monoxide (eCO) will be measured, by an eCO monitor, in every scheduled pregnancy visit.

12 months after the basal visit (when participants receive counsel to quit smoking), smoking habit will be evaluated and those participants reporting smoking abstinence, eCO and urinary cotinine tests will be performed.

Lost to follow-up will be considered [1] when the participant decide to quit the study, [2] when the participant do not attend one of the visits and is impossible to contact with them by telephone call and, [3] when pregnancy follow-up is derived to another healthcare unit (high risk obstetric) or another centre.

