## Methods

### Study objectives

The primary objective of this research is to evaluate the effectiveness of an intervention against tobacco in pregnant smokers based on the Tobbstop App, which has already been validated for smoking cessation in the general population [19, 20].

The specific objectives which have set out are:To determine the effectiveness of the intervention on smoking cessation during pregnancy.To evaluate the effectiveness of the intervention on prolonged abstinence.To analyse the impact of the intervention to reduce daily consumption in pregnant smokers who continue smoking.To determine the impact of the intervention on pregnancy, birth and neonatal health indicators.

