#### Exclusion criteria

Consonant smokers or in the Pre-contemplation stage, according to Prochaska and DiClemente’s model [23].Having participated in a smoking cessation study within the last 12 months.Psychiatric history that prevents or limits follow-up of the study.Having another substance dependence or abuse, apart from tobacco consumption.Currently under a smoking cessation treatment.Impossibility of follow-up participation for any reason.Patient refusal to participate or withdrawal from the study.

(*) It is understood that you have skills on the use of Apps and willingness to use them if you answer affirmatively to the following questions:i.Have you downloaded any application on your mobile?ii.Would you install an application to help you quit smoking on your mobile?iii.Have you participated in any chat group?iv.Have you played any game with your mobile device? (Criteria to ensure the usability of the intervention tool).

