#### Statistical analysis

The efficacy of randomisation will be tested by assessing the comparability and homogeneity of the groups in terms of the similarity of the distribution of the variables of interest at baseline. In addition, the proportion of losses in each group during follow-up will be quantified and assessed as to whether these are independent of the study intervention.

Analysis will be performed as intention to treat. To assess the theoretical bias due to loss to follow-up will be assessed using the 'worst-case analysis' strategy, which will assume that lost patients (in both groups) continue smoking. In case of reporting abstinence but not presenting at the final follow-up visit, self-reported but unconfirmed abstinence will be considered.

Standard statistical tests will be used to analyse the described continuous and categorical variables (e.g. mean, standard deviation, proportions, etc.). Continuous variables will be compared using the Student’s t-test when following a normal distribution or using the U-Man Whitney test if variables are not normally distributed. For categorical variables, Pearson's chi-square test will be used. Point abstinence rates at the end of pregnancy and prolonged abstinence, 12 months after the intervention, will be compared between both groups.

To assess the effectiveness of implementation, odds ratios of association between the allocation group and prolonged abstinence will be calculated. Odds ratios will be calculated crude and adjusted for clinically relevant covariates and relevant interactions between them. Survival analysis will also be carried out for prolonged abstinence at 12 months from counselling smoking cessation. A multivariate Cox regression analysis will be performed comparing the two groups using the Log-Rank test to calculate the Hazard Ratio for abstinence at the end of pregnancy and prolonged abstinence at 12 months after the intervention.

The relationship between missing data and the main variables will be analysed. If missing values exceed 3%, the possibility of applying missing imputation techniques will be studied.

All statistical analysis tests will be conducted with R Statistics package (R foundation for statistical computing, Vienna, Austria; version 4.1.2 or later) and will be considered significant when *p* < 0.05.

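### The loss-to-follow-up definition counts transferred women as lost even if they can still be telephoned and tested, gives no way back after one unreachable missed visit, and leaves their smoking status open to two readings

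*Protocol article*

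**What the plan says.** Follow-up and data collection gives three routes to being lost:

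1. Quitting: "Lost to follow-up will be considered [1] when the participant decide to quit the study".
2. One missed contact: "when the participant do not attend one of the visits and is impossible to contact with them by telephone call".
3. Transfer of care: "when pregnancy follow-up is derived to another healthcare unit (high risk obstetric) or another centre".

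No sentence says that a woman lost by route 2 or 3 can return, or that calls to her continue. The same section plans monthly telephone interviews after the birth. It also plans a smoking assessment 12 months after the basal visit, with exhaled CO and urinary cotinine for women who report abstinence.

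Statistical analysis states "Analysis will be performed as intention to treat". It adds a worst-case strategy for assessing bias from loss, "which will assume that lost patients (in both groups) continue smoking". For women who report abstinence but do not come to the final visit, "self-reported but unconfirmed abstinence will be considered". Losses are to be quantified by group, and imputation may be studied if missing values exceed 3%.

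Exclusion criteria lists "Patient refusal to participate or withdrawal from the study". One specific objective is "To determine the impact of the intervention on pregnancy, birth and neonatal health indicators". Data recording and storage takes birth and newborn data from the primary care record (e-CAP), while Table 1 places those indicators at the usual pregnancy visits.

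**The concern.** Loss to follow-up should mean that the outcome could not be obtained. Route 3 defines it by where pregnancy care is given. A transferred woman may answer every call and be willing to give a breath and urine sample at 12 months, yet she is lost. Route 2 makes one failed contact final, although later calls and the 12-month visit could still reach her.

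Two things are at stake. First, an obtainable primary outcome may be replaced by an assumption, and the text does not settle which assumption applies. Second, referral to a high-risk unit happens after randomisation and is linked to complications, which are the subject of the pregnancy, birth and neonatal objective. Loss by this route need not be random and could differ between groups.

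Listing withdrawal as an exclusion criterion adds a smaller inconsistency: one section calls it an exclusion and another calls it a loss.

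**Working it through.** **Is the outcome obtainable after transfer?** Women enter while pregnant (before 28 weeks), so 12 months after the basal visit falls after the birth, when pregnancy care has ended. Contact after birth is by telephone and does not depend on the unit that gave the care. Before birth, the protocol already substitutes a call for a missed visit. Nothing in the planned 12-month assessment requires that pregnancy care stayed at the recruiting centre.

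**How is a transferred woman scored if she reports abstinence by telephone and does not attend the final visit?**

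| Sentence applied (Statistical analysis) | Her status |
|---|---|
| Lost women continue smoking | Smoker |
| Unconfirmed self-report is considered | Abstinent |

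Both sentences cover her, and no order of precedence is given.

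**How is a woman who withdraws handled?** She is lost under Follow-up and data collection, and assumed to smoke in the worst-case analysis under intention to treat. Exclusion criteria names the same event as a reason for exclusion.

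**The plan's own sample size.** Inputs from Sample size/power calculation: 0.50 v 0.65, two-sided alpha 0.05, power 0.80, arcsine method, 5% loss, 200 per group.

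- h = 2·asin(√0.65) − 2·asin(√0.50) = 0.3047
- n = 2·((1.960 + 0.842)/0.3047)² = 169.1, so 170 per group
- with 5% loss: 170/0.95 = 178.9, so 179

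The stated 200 is not reproduced. It equals 170/0.85, a 15% allowance. The difference is on the safe side (power at 200 per group is 86.1%) and is a separate matter.

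**Cumulative loss by route 2 alone (illustrative).** Assumptions: k = 8 to 15 contacts, because Figure 2 is not shown; the same chance p at each contact of being both missed and unreachable; independence between contacts. Loss = 1 − (1 − p)^k.

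| p per contact | k = 8 | k = 12 | k = 15 |
|---|---|---|---|
| 1% | 7.7% | 11.4% | 14.0% |
| 2% | 14.9% | 21.5% | 26.1% |

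Staying within 5% needs p = 1 − 0.95^(1/k), which is 0.64% at k = 8 and 0.34% at k = 15, before any withdrawals or transfers.

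**Power at 200 per group.** If a fraction d is lost in each group and scored as smoking, the rates become 0.50(1 − d) and 0.65(1 − d). Power = Φ((difference − 1.96·SE₀)/SE₁), with SE₀ pooled and SE₁ unpooled. At d = 5% the rates are 0.475 and 0.6175, SE₀ = 0.0498 and SE₁ = 0.0493, so power = Φ(0.912) = 81.9%.

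| Loss in each group | Lost = smoker | Lost left out |
|---|---|---|
| 5% | 81.9% | 84.4% |
| 10% | 77.3% | 82.4% |
| 15% | 72.4% | 80.2% |

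**Unequal loss, lost = smoker (illustrative).** With 5% control and 10% intervention: 0.65 × 0.90 − 0.50 × 0.95 = 0.585 − 0.475 = 11.0 points instead of 15, and power is about 60%. With 10% control and 5% intervention: 0.6175 − 0.450 = 16.75 points.

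**The case against.** Much can be said for the plan, and several stronger readings that a reader might infer do not hold.

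- **That birth and newborn data go missing for complicated pregnancies.** Not established. These data come from e-CAP, separately from the visit questionnaire, and nothing says that extraction stops for women labelled lost. What stands is a risk: the article does not say that extraction continues or whether e-CAP covers births managed elsewhere.
- **That withdrawn women are dropped from the analysis.** Less supported than the alternative. Participant selection applies the exclusion list when women are invited, and the other two sections treat quitting as a loss under intention to treat. The wording is loose and should be aligned.
- **That a lost woman counts as smoking whatever she does.** The assumption is presented as an assessment of bias from loss, and it is not clear that it is the primary analysis. Unconfirmed self-report and imputation are also mentioned. What stands is that the rules overlap.
- **That route 2 discards reachable women.** It requires failed telephone contact, so they are unreachable at that moment. What stands is the missing way back.
- **That the 5% allowance cannot hold.** Not shown. It holds if misses are rare enough, and misses concentrated in the same women would give less cumulative loss than the independence formula.

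The plan also compares losses between groups. That could detect selective loss but would not recover the outcomes. A condensed article may leave re-contact procedure to the full protocol, but the transfer rule is stated outright and is not a missing detail.

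**Conclusion.** The concern holds in a limited form. The transfer rule is the firm part: followed as written, it labels a woman lost for a post-randomisation event linked to complications, when the planned calls and 12-month assessment could still give her outcome. The overlap between the smoking assumption and the self-report rule is also in the text and bears on the primary endpoint.

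The size is uncertain. The share of women transferred is not given, and the number of contacts is assumed. The power figures further assume that lost-as-smoker is the analysis used and that 0.50 and 0.65 are rates before any loss. The documents settle neither. If the stated 5% is met, power stays above 80% either way. At 10% or 15% it falls below 80% only when lost women are scored as smokers. The unequal-loss figures show sensitivity; the documents give no direction for such a difference.

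This should be fixed. It is not shown to invalidate the trial.

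**What to change.** - Define loss outcome by outcome. For the primary outcome, a woman is lost only if no 12-month smoking assessment is obtained.
- Keep telephoning women who transfer care or miss a contact, and invite them to the 12-month visit, unless they withdraw consent.
- State which rule takes precedence when a woman reports abstinence but does not attend the final visit.
- State that e-CAP birth and newborn data are still extracted for transferred and missed women where available.
- Remove withdrawal from the exclusion criteria and keep women who withdraw in the intention-to-treat denominator, in line with the other two sections.

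The cost is a change of wording, a little extra tracing, and inviting transferred women back for the final test. The calls, the final visit and the record extraction are already planned. The change is best made early, because contacts that were never attempted are hard to recover.

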### Data recording and storage

The information from the study will be registered and stored in three different platforms:Data obtained during the basal and follow-up visits will be registered in a data collection questionnaire (designed specifically for this purpose) and stored in an application accessible from the corporate Intranet of the ICS. Access to this website is restricted and will be controlled by a personal password for each researcher, who will be responsible for entering the records of the participants recruited.Data related to clinical history about patient, birth and new-born will be extracted from the Primary Care computerized clinical history (e-CAP).Data about App usability, daily smoking progression, emotions, and chat participation, will be extracted from the App and stored in a local service from the URV.

### Outcomes assessment

The main outcome variable will be prolonged abstinence at 12 moths, and the secondary variable will be 3-months and 6-monts prolonged abstinence, and punctual abstinence. The criteria for establishing abstinence have been defined according to the recommendations of the Society for Research on Nicotine and Tobacco [24]:Continuous abstinence: sustained abstinence from the time of intervention to a follow-up period.Prolonged abstinence: sustained abstinence between an initial grace period (^$^) and a follow-up period.Punctual abstinence: abstinence during a window of time (usually 7 days) immediately preceding the time of follow-up.

(^$^) Grace period is the period immediately following the defined quit date or intervention date in which continued smoking is not counted as failure. For most studies it is recommended to be no longer than 2–4 weeks.

To confirm self-reported abstinence, eCO and urine cotinine tests will be taken 12 months after the basal visit. The cut-off point of expired-CO levels is 10 ppm, as lower values indicate non-smoking and higher values indicate smoking in the previous 12–24 h [22]. Urine cotinine values less than 100 ng/mL will reflect an abstinence condition, values between 100 and 500 ng/mL will be accepted as occasional smoker, and values above 500 ng/mL will be considered as smoker [25].

Thus, only those participants reporting smoking abstinence and having eCO levels less than 10 ppm and urine cotinine values less than 100 ng/mL will be considered non-smokers.

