**Confirmation of smoking abstinence:**				
eCO test		X^*$*^		X^*$*^
Cotinine test in urine				X^*$*^

If the telephone visit and the face-to-face visit coincide, the telephone visit will be omitted

*Relapse. In case of relapse, the following data should be collected: the presence of withdrawal symptoms, if she is still taking the prescribed treatment and if she has smoked a puff

^*$*^eCO and cotinine tests will be taken only to confirm the smoking abstinence reported by the participant

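### The 12-month abstinence rule applies a urine cotinine cut-off without regard to nicotine source, so it can score an abstinent woman still using nicotine replacement as a smoker

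*Protocol article*

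**What the plan says.** The Outcomes assessment section of the protocol article gives a closed rule at 12 months. Of the women who say they have stopped, only those "having eCO levels less than 10 ppm and urine cotinine values less than 100 ng/mL will be considered non-smokers". It reads higher cotinine as smoking without asking where the nicotine came from: "values between 100 and 500 ng/mL will be accepted as occasional smoker, and values above 500 ng/mL will be considered as smoker". Table 2 repeats the bands and schedules cotinine at the end of the study only.

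The same article expects that cessation drugs may be used after entry. Table 2, under Smoking habit, has the variable "Use of drug therapy or other methods for smoking cessation during the study", scheduled at basal and follow-up, with the categories "Nicotine replacement therapy; Bupropion; Varenicycline; Others". The exclusion criterion "Currently under a smoking cessation treatment" applies at entry, and nothing in the article bars starting such treatment later. The Table 1 footnote on relapse also asks "if she is still taking the prescribed treatment and if she has smoked a puff".

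The only stated departure from biochemical confirmation is in the Statistical analysis section. It lets unconfirmed self-report be considered for abstainers who do not come to the final visit.

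**The concern.** The outcome is abstinence from smoking, not from nicotine. Cotinine is a metabolite of nicotine and cannot separate medicinal from smoked nicotine. This is general pharmacology, which the article does not state. The three conditions are joined by *and*, so a woman who reports abstinence and has eCO below 10 ppm still fails if medicinal nicotine takes her cotinine to 100 ng/mL or more. The protocol collects the variable that would explain such a result but never links it to the outcome.

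The rule can also treat like cases differently. A nicotine replacement user who misses the final visit may keep her self-reported abstinence, while an identical woman who attends may be scored a smoker.

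At stake are true successes counted as failures on the primary outcome. Equal use across arms lowers both rates and costs power. Unequal use would bias the comparison.

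**Working it through.** **Inputs from Sample size/power calculation:** rates 0.50 (control) and 0.65 (intervention), two-sided alpha 0.05, beta below 0.2, 200 per group, 5% loss, arcsine approximation. Evaluable per arm: 200 × 0.95 = 190.

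**Assumed, not in the article:** f0 and f1, the shares of true abstainers in the control and intervention arms who attend at 12 months while using nicotine replacement and have cotinine of at least 100 ng/mL, taken as 0 to 20%. Also assumed: 0.50 and 0.65 are true rates before verification.

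**1. The plan's own figure.** n = (1.960 + 0.8416)² / [2(asin√0.65 − asin√0.50)²] = 7.849 / [2 × (0.937744 − 0.785398)²] = 169.1, so 170 per group. With 5% loss, 170/0.95 gives 179. The stated 200 is not reproduced; it equals 170/0.85, a 15% loss. It errs on the safe side and has no bearing on the cotinine rule.

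**2. Power without misclassification.** Power = Φ(h√(n/2) − 1.960), with h = 2(asin√p1 − asin√p0) = 0.3047. At n = 190, √95 = 9.747, so Φ(2.970 − 1.960) = Φ(1.010) = 84.4%.

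**3. Effect of the rule.** Observed rate = true rate × (1 − f). For 5% in both arms: 0.50 × 0.95 = 0.475 and 0.65 × 0.95 = 0.6175; h = 0.2872; power = 79.9%. In women per 200 randomised, that is 200 × 0.50 × 0.05 = 5 in control and 200 × 0.65 × 0.05 = 6.5 in intervention.

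| f0 | f1 | Observed rates | Difference (points) | Odds ratio | Chance of significance, n = 190 |
|---|---|---|---|---|---|
| 0 | 0 | 0.500 vs 0.650 | 15.0 | 1.857 | 84.4% |
| 2% | 2% | 0.490 vs 0.637 | 14.7 | 1.826 | 82.6% |
| 5% | 5% | 0.475 vs 0.6175 | 14.25 | 1.784 | 79.9% |
| 10% | 10% | 0.450 vs 0.585 | 13.5 | 1.723 | 75.2% |
| 20% | 20% | 0.400 vs 0.520 | 12.0 | 1.625 | 65.3% |
| 5% | 10% | 0.475 vs 0.585 | 11.0 | 1.558 | 57.6% |
| 10% | 5% | 0.450 vs 0.6175 | 16.75 | 1.973 | 90.8% |

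With 200 analysed per arm, the 5%/5% case moves power from 86.1% to 81.9%. The last two rows are mirror images: the first shrinks the App effect and the second inflates it. The article gives no reason to prefer either.

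**The case against.** Most of the case on the other side concerns scope and size, and much of it stands.

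- **Few women are exposed.** Cotinine is taken once, 12 months after the basal visit, and only from self-reported abstainers who attend. The Background says pregnant smokers seldom ask for behavioural support or pharmacotherapy, and neither arm is described as supplying nicotine replacement. A reader might infer that the rule misclassifies abstinent women at large; the article does not support that.
- **The Table 1 footnote is weak support.** It applies to women who relapse and does not name the treatment. The point rests on Table 2 instead.
- **A difference between arms is conjecture.** Both arms receive the same counselling, and App access ends 90 days after the quit day. A reader might take the 57.6% row as the likely power, or conclude that the App is disadvantaged. That row needs an asymmetry for which the article gives no basis, and its mirror image favours the App.
- **The planned rates may already be verified rates.** The article does not say. If they are, the planned power already allows for the rule and none is lost.
- **The strict rule is conservative, and exempting users has a price.** The article says eCO reflects the previous 12–24 h, and its Discussion acknowledges that pregnant smokers misreport. Table 2 counts e-cigarettes and smokeless tobacco as tobacco consumption, which eCO would not detect. This stands as a reason to report both rules.
- **The detail may sit in the full protocol or analysis plan.** This does not dispose of the point: the article states a complete rule, introduced by *only*, and as stated it can give a wrong outcome for a group the article foresees.

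**Conclusion.** The point holds in a limited form. As written, the rule can score as smokers those self-reported abstainers who attend the 12-month visit while still using nicotine replacement at a level that takes urine cotinine to 100 ng/mL or more. The number of such women is probably small and cannot be derived from the protocol.

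Equal use in both arms lowers both rates. At an assumed 5% of abstainers, power falls by about 4 to 5 points, to roughly the planned 80%, provided 0.50 and 0.65 are rates before verification. Unequal use could bias the App effect either way, but neither the direction nor the presence of such bias can be asserted. The point does not invalidate the design. It should be settled before outcome data are seen, because a later choice would be a post hoc change to the primary endpoint.

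**What to change.** In Outcomes assessment, add that for women with nicotine replacement use recorded at the 12-month visit, abstinence is confirmed by self-report plus eCO below 10 ppm, and that cotinine below 100 ng/mL remains required for all others. Report the cotinine-for-all result alongside as a sensitivity analysis.

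Confirm that the Table 2 drug-therapy variable is captured at the 12-month visit itself. Its schedule reads basal and follow-up, whereas eCO is listed for follow-up and end, and cotinine for end.

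The cost is a sentence or two and, if the variable is not yet collected at that visit, one questionnaire item. No extra test is needed and no treatment changes. The downside is that eCO has a short window and does not detect non-combusted tobacco, so some false abstainers may be accepted in this subgroup. For these women the two rules bracket each arm's abstinence rate, because one counts those with cotinine of at least 100 ng/mL as failures and the other counts them as successes if self-report and eCO agree. Giving the number of such women by arm would let readers judge the effect on the comparison.
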